### Secondary outcome measures

As a secondary target criterion, the decrease in depression is recorded by the MADRS [47] and the second edition of BDI-II [43].

The MADRS [47] is a measure of change in depression. It contains 10 items which are scored from 0 to 6. Each item has its specific meaning for the rating, e.g. the item ‘Inability to feel’ is scored from 0 = “Normal interest in the surroundings and other people” to 6 = “The experience of being emotionally paralyzed, inability to feel anger, grief or pleasure and a complete or even painful failure to feel for close relatives and friends”. Another example item is reduced appetite, scored from 0 = “Normal or increased appetite” to 6 = “Needs persuasion to eat at all”. The MADRS has shown good validity, *r* = 0.63 and reliability, *α* = 0.85 [50].

The BDI-II [43] is a widely used scale of depression symptoms. It contains 21 self-report items which are scored from 0 to 3, with 3 being the highest severity. Example items include Crying, scored from 0 = “I don’t cry more often than I used to” to 3 = “I feel like crying, but I can’t” and Worthlessness, scored from 0 = “I do not feel I am worthless” to 3 = “I feel utterly worthless”. The BDI-II has been evaluated as valid *d* = 0.80 and reliable, *α* = 0.89 [51].

Improvement in general functional level in the verum vs. sham group is measured by the GAF [44]. The GAF describes an individual’s general functioning on a broad spectrum of activities in 10 steps, which each contain 10%, meaning an individual can score the lowest functional level of 1–10% meaning a persistent danger to self or others, a persistent inability to care for yourself or performed a serious suicidal act. The highest achievable level, 91–100%, no symptoms present, excellent functioning in a wide range of activities as well as good social standing due to self-presentation and a good handling of life obstacles. The GAF has been found to be reliable, *r* = 0.54 to 0.66 [52] and showing good discriminant validity, *r* = 0.63 [53].

A decrease in impulsivity is recorded by the BIS-15 [45]. The BIS-15 is a measure used for the identification of impulsive acts. It contains 15 items scored from 1 = ”Rarely/Never” to 4 = “ Almost Always/Always”. Example items include “I say things without thinking” and “I don’t pay attention”. The BIS-15 has been found to be valid, *r* = 0.37 = and reliable *α* = 0.81 [54].

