### Intertemporal decision-making task (delay discounting)

Changes in impulsivity will be assessed by a cognitive task (delay discounting).

Delay discounting as a representative characteristic of impulsive behavior is especially important in BPD, which is often described as an impulse control disorder [56]. Krause-Utz et al. [57] found that delay discounting might be considered a general feature of BPD, with individuals affected by it showing a higher degree of delay discounting even when controlling for comorbid ADHD. The researchers also concluded that the number of induced stressors did not influence the degree of delay discounting in BPD individuals. This means that the degree of delay discounting is likely not influenced by external factors, but generally present in affected individuals.

The delay discounting paradigm is a very common way of measuring impulsiveness and self-control. The variant we are going to use was developed by Kirby et al. [48] and has already been validated in numerous clinical populations (e.g. in addiction disorders [48]; depression [58]; and schizophrenia [59]). In the assignment, patients will be asked to make a series of decisions where they have to choose between a small reward on the same day or a larger reward that is paid out after a waiting period. The task will include 27 rounds with different amounts of money (11–85 €) and different waiting times (7–186 days). At the end of the experiment, one of these 27 rounds will be randomly selected and the patients will be paid 10% of the chosen amount of money. If the patients have opted for the immediate reward in the selected round, they will receive the money on the same day. If a decision is made in favor of the later reward, the money will either be sent by post or, if the time is still during the inpatient stay, the patients will receive the money from the ward staff on the specified day. Since the patients complete the task twice, they can earn between 2.20 and 17 €.

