### Data analysis

Regarding therapy response, a 2 × 2-factorial between-subjects design with the between-subject factor stimulation (TMS vs. Sham) and the within-subject factor time (T0 vs. T1) will be conducted. To deal with a possible bias by treatment drop-out, a Linear Mixed Repeated Measure Model approach will be applied considering all assessed timepoints and the primary outcome (differences in BSL-23 reduction over time between study groups, i.e. interaction time*group) will be tested for significance (p ≤ 0.05). In case of relevant pre-treatment differences, these will be included in the model as covariates to adjust for. Likewise, secondary outcomes will analyzed accordingly.

In a second step, patients will be grouped into responder and non-responder. Group assignment will be performed post-hoc and based on the Reliable Change Index (RCI) as suggested by Jacobson and Truax [64]. An RCI above the 95% confidence limits (+/= 1.96) indicates a reliable change (p < 0.05). To identify parameters which are relevant for therapy response, group comparisons will be performed on secondary outcome variables of T0, using MANOVA models with the independent factor therapy response (responder vs. non-responder) and secondary outcome variables of T0 as dependent variables. Analyses will be corrected for multiple comparisons using Bonferroni Correction and partial eta-square will be determined to report effect size.

Analyses will be conducted with IBM SPSS [65].

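### The stated correction is plain Bonferroni; Holm controls the same familywise error and never rejects less, so it should replace Bonferroni wherever that sentence applies

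*Protocol article*

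**What the plan says.** All of this stands in the Data analysis section of the protocol article unless noted.

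- The first paragraph tests the primary outcome, the time-by-group interaction on the BSL-23, at p ≤ 0.05. It then adds: "Likewise, secondary outcomes will analyzed accordingly". No adjustment is named there.
- The next paragraph opens with "In a second step, patients will be grouped into responder and non-responder". It describes a post-hoc grouping by the Reliable Change Index and MANOVA models on the T0 values of the secondary outcomes.
- That paragraph ends with the only multiplicity rule in the document: "Analyses will be corrected for multiple comparisons using Bonferroni Correction and partial eta-square will be determined to report effect size". Its subject is not limited to the MANOVA.
- Under Secondary outcome measures five scales are described: MADRS and BDI-II ("the decrease in depression is recorded by the MADRS [47] and the second edition of BDI-II [43]"), GAF, BIS-15 and SCS-D. The delay discounting task has its own section, where it is introduced with "Changes in impulsivity will be assessed by a cognitive task (delay discounting"). It has no row in the assessment schedule (Table 1).
- The Discussion calls the research question exploratory and the study a pilot that prepares a later confirmatory trial.

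**The concern.** Bonferroni holds every test to 0.05/k, however many of the other hypotheses have already been rejected. A step-down version relaxes the threshold after each rejection without loosening the error guarantee. With about 40 evaluable patients, keeping the stricter rule gives up true findings and gains nothing in error control.

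The reach of the sentence is also open. One analyst could apply the correction only to the responder comparisons, and another to the randomised secondary tests as well. Both could say that they followed the plan, yet they would use different thresholds on the same data.

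**Working it through.** **Inputs.** From the documents: alpha 0.05; 40 evaluable patients with 1:1 allocation, hence 20 per group; five secondary scales, or six tests if delay discounting is counted. Assumed, because the documents do not give them: a standardised effect d = 0.8, the correlation between test statistics, and normally distributed statistics. The plan states no familywise error rate, so there is no figure of its own to reproduce.

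**Step 1: Holm never rejects less.** Order the k p-values from smallest to largest. Bonferroni compares each with 0.05/k. Holm compares the i-th smallest with 0.05/(k − i + 1) and stops at the first failure. For k = 6 the Holm thresholds are 0.0083, 0.0100, 0.0125, 0.0167, 0.0250 and 0.0500; Bonferroni uses 0.0083 throughout. Every Holm threshold is at least 0.05/k, so any p-value that passes Bonferroni passes Holm.

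**Step 2: the error guarantee is the same.** Suppose m of the k null hypotheses are true. When Holm first reaches a true null, at most k − m hypotheses have been rejected, so the threshold there is at most 0.05/m. The chance that any of the m true nulls falls below 0.05/m is at most m × 0.05/m = 0.05, whatever the correlation. Simulated with all six nulls true, both methods give 4.9% at correlation 0 and 3.3% at 0.7.

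**Step 3: power.** The noncentrality is 0.8/√(2/20) = 0.8/0.316 = 2.53. The Bonferroni critical value for 0.05/6 = 0.0083 two-sided is 2.64, so power per test is Φ(2.53 − 2.64) ≈ 0.457. Uncorrected, it is Φ(2.53 − 1.96) ≈ 0.716. Simulated mean power per true effect, six tests:

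| True effects | Correlation | Bonferroni | Holm |
|---|---|---|---|
| 1 | 0.5 | 45.6% | 45.6% |
| 3 | 0.4 | 45.7% | 48.2% |
| 6 | 0.4 | 45.8% | 55.3% |

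The result hardly depends on the correlation: with six true effects the pair is 45.7% and 55.1% at correlation 0, and 45.6% and 54.7% at 0.7. With five tests at correlation 0.5 it is 48.3% and 51.6% for three true effects, and 48.0% and 57.1% for five. The gain lies in the second and later rejections. The chance of at least one rejection is practically the same for both methods (82.5% each with six true effects at correlation 0.5).

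**Step 4: if the sentence does not reach the secondary tests.** With k independent tests at 0.05 each, the chance of at least one false positive when iTBS has no effect on any of them is 1 − 0.95^k: 22.6% for five and 26.5% for six. With correlation, by simulation:

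| Tests | 0 | 0.3 | 0.5 | 0.7 |
|---|---|---|---|---|
| 5 | 22.6% | 20.8% | 18.3% | 14.9% |
| 6 | 26.5% | 24.2% | 20.8% | 16.3% |

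The range is therefore about 15% to 27%. If Bonferroni does cover six independent tests, the figure is 1 − (1 − 0.0083)^6 = 4.9%.

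**The case against.** Bonferroni is valid, so one may call the choice between it and Holm a matter of taste. That does not quite stand. Holm gives the same guarantee under the same absence of assumptions and rejects at least as much. One thing Bonferroni offers beyond Holm is simple simultaneous confidence intervals, and the article does not plan these; it reports partial eta-squared. What does stand is that the gain is modest: about 2.5 points with three true effects, and practically none with one.

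It may also be said that handling of secondary outcomes belongs in the analysis plan, which is not shown. That is fair for rules on which the article is silent. It does not cover a rule that the article states.

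Two stronger readings are tempting and are not supported:

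- **The secondary claims are unprotected, with a one-in-four chance of a false one.** This takes one reading of an ambiguous sentence as fact. If the unqualified subject includes the secondary tests, their error is already controlled. The reference back to the primary analysis may concern only the model, since p ≤ 0.05 is attached to the primary outcome. The count of six is inferred, and one in four is the upper end of the range. Nowhere does the article say that a benefit will be declared from any single significant scale.
- **Holm both repairs the error rate and adds power.** For the same tests these cannot both hold. If the tests are now uncorrected, Holm lowers power per true effect from about 72% to 48–55% in the setting above with three to six true effects. If they are now under Bonferroni, the error rate needs no repair.

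**Conclusion.** The point holds in a limited form. Wherever the Bonferroni sentence applies, Holm at 0.05 is better: same familywise error under any correlation, never fewer rejections, and power per true effect of 48% against 46% (three true effects) or 55% against 46% (six). These power figures assume six tests, 20 per group, d = 0.8, correlation 0.4 and normal statistics. In the responder comparison the group sizes depend on how many patients respond, so there the figures show direction and rough size only.

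If the sentence does not cover the randomised secondary tests, a familywise error of about 15–27% is not in itself an error in the plan. There is a single primary outcome, whose type I error these tests do not touch, and the study is an exploratory pilot. Unadjusted secondary tests are then acceptable, provided that they are reported as exploratory. The article does not settle which case applies.

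**What to change.** In the closing sentence of the responder paragraph, replace the Bonferroni correction by the Holm step-down procedure at a familywise level of 0.05, and name the set or sets of tests to which it applies. Holm needs only the ordered p-values; it takes no further data and costs no power relative to Bonferroni.

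In the same place, say whether the randomised secondary time-by-group tests are in that set. If they are, list them and state whether delay discounting is one of them. If they are not, state that they are exploratory and will be reported as estimates with 95% confidence intervals. Bringing them under familywise control when they are now meant to be uncorrected is a real trade-off: it would cost power per test, as shown above, and is not required in a pilot.

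The change takes one or two sentences and should be fixed before the group allocation is revealed to the analysts.

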Due to the exploratory nature of our research question, the design will be conducted as a pilot study. It will provide evidence for feasibility and effect-size measures that allow for a data-based decision on the implementation, design and sample-size calculation of a confirmative multi-center trial. Our results might deliver answers to the questions if and how future studies should further investigate an enhancing effect of iTBS as an add-on to DBT or any other evidence-based psychotherapy in the treatment of BPD patients. Besides, we can identify necessary precautions and additional steps that can be taken to enhance the quality of further investigations. Furthermore, our study serves as an important addition to prospective investigations of DBT in a clinical setting itself.

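### In the post-hoc responder MANOVA the named effect size, partial eta-squared, is unsigned and biased upward: with no true difference its omnibus value still averages about 0.10 to 0.15

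*Protocol article*

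**What the plan says.** The Data analysis section of the protocol article has two steps.

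- **Step 1, treatment effect.** "a Linear Mixed Repeated Measure Model approach will be applied considering all assessed timepoints", and the time-by-group interaction on BSL-23 is tested. This paragraph names no effect-size measure.
- **Step 2, response.** Patients are classed as responders or non-responders by the Reliable Change Index, and the two groups are compared at baseline, "using MANOVA models with the independent factor therapy response (responder vs. non-responder) and secondary outcome variables of T0 as dependent variables". The paragraph ends by announcing a Bonferroni correction and that "partial eta-square will be determined to report effect size".

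Partial eta-squared is the only effect-size measure named for reporting results. Cohen's d and f appear only in the sample-size section. The Discussion expects the pilot to supply "effect-size measures that allow for a data-based decision on the implementation, design and sample-size calculation" for a confirmatory trial.

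**The concern.** Step 2 is meant to find baseline characteristics that matter for response. For that purpose a reader needs to know which group scored higher, by how much, and whether the figure exceeds what chance alone would give. Partial eta-squared answers none of these well at this sample size. It has no sign and no scale units. Because it is bounded below by zero, its expected value is positive even when the groups do not differ, and the excess grows with the number of dependent variables.

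The sample-size section itself warns that small studies can overestimate effects. A metric that overestimates before any selection on significance sits badly with that warning. What is at stake is limited: the weight readers give to candidate predictors of response.

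**Working it through.** **Inputs**

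- Number of dependent variables, p. Under Secondary outcome measures: MADRS, BDI-II, GAF, BIS-15 and SCS-D, so p = 5. Delay discounting has its own heading; counting it gives p = 6.
- Number of patients, N. The sample-size section gives 40 analysable and 53 enrolled with a 25% dropout allowance (40/0.75 = 53.3). Patients who miss more than four sessions are excluded and all others are kept, so N is taken as 40 to 53.
- Planning effect: f = 0.2.

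**The plan's own reference value.** The article states no partial eta-squared. Its planning effect converts as f²/(1+f²) = 0.04/1.04 = 0.038.

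**Distribution under no difference.** With two groups, the multivariate partial eta-squared equals 1 minus Wilks' lambda. If responder status is unrelated to the baseline scales, this follows Beta(p/2, (N-p-1)/2), with mean p/(N-1).

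| Scales in one model | N | Null mean | 95th percentile |
|---|---|---|---|
| 6 | 40 | 6/39 = 0.154 | 0.30 |
| 5 | 40 | 5/39 = 0.128 | 0.27 |
| 6 | 53 | 6/52 = 0.115 | 0.23 |
| 5 | 53 | 5/52 = 0.096 | 0.20 |
| 1 | 40 | 1/39 = 0.026 | 0.10 |
| 1 | 53 | 1/52 = 0.019 | 0.07 |

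A simulation of 20,000 data sets with scales correlated 0.4 agreed: for six scales and N = 40 the mean was 0.154, both with a 20/20 and with a 12/28 split.

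**How often noise looks like an effect.** From the same Beta distribution, half of null data sets (0.51) give 0.14 or more with six scales and N = 40. In the most favourable omnibus case (five scales, N = 53), 70% give 0.06 or more.

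**On the f scale.** With f = √(η²/(1-η²)), the null mean 0.096 corresponds to √(0.096/0.904) = 0.33, and 0.154 to √(0.154/0.846) = 0.43. The planning value is 0.2. This compares scale only, since f = 0.2 was set for a different test.

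**With a real difference.** For a true value of 0.06, six scales and N = 40, the expected report is about 1 - 0.94 × 33/39 = 0.20; simulation gave 0.204.

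**Bias-adjusted form.** The formula 1 - (1-R²)(N-1)/(N-p-1), evaluated at R² = p/(N-1), gives exactly zero. For example, 1 - (1 - 6/39) × 39/33 = 0.

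**The case against.** The strongest reply is that partial eta-squared is a standard MANOVA measure, that all statistics of the R-squared type share this bias, and that the analysis is post-hoc in a declared exploratory pilot. No primary inference depends on it, and the figure would appear beside a Bonferroni-corrected test. All of this stands, and it is why the point is minor.

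Three further objections also limit it.

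- **The 0.15 is the top of the range.** It needs delay discounting as a sixth scale and exactly 40 patients. The article speaks of models in the plural and does not say that all scales enter one of them; two scales at N = 40 would give 2/39 = 0.05.
- **Single-scale values may serve the aim better.** Their null mean is only about 0.02 to 0.03. That is still not negligible beside 0.038.
- **Naming this metric does not exclude group means or intervals.** A condensed article may leave those to the full plan, so their absence is no error. The criticism is of the metric that is named.

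A reader might infer from the Discussion that the effect sizes intended for the confirmatory trial are themselves inflated. The documents do not support that. The sentence on partial eta-squared closes the responder paragraph, whereas a confirmatory trial would be sized on iTBS versus sham. That contrast comes from the mixed model, which yields a signed estimate in BSL-23 points. The opening word of the sentence could be read as covering every analysis, but its position favours the narrower reading.

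**Conclusion.** The point holds for the responder versus non-responder comparison only. There, the named effect size carries no direction and is materially biased upward: its omnibus null mean is 0.096 to 0.154 for five or six scales and 40 to 53 patients, and 0.019 to 0.026 for a single scale. The omnibus figures are about 2.5 to 4 times the 0.038 that matches the planning effect (0.096/0.038 = 2.5; 0.154/0.038 = 4.1).

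These figures assume normally distributed scales, complete baseline data, and responder status unrelated to baseline under the null. The omnibus figures also assume that all scales enter one model. Severity: minor.

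**What to change.** In the Data analysis section, replace partial eta-squared for the responder comparison. For each T0 scale, report the signed mean difference between responders and non-responders with its 95% CI, and Hedges' g.

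If an explained-variance figure is kept, use a bias-adjusted form (omega- or epsilon-squared), for example 1 - (1-R²)(N-1)/(N-p-1), and state how many scales enter the model. Report negative values as they fall, because setting them to zero brings back part of the bias.

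The cost is one sentence and no new data. The downside is that the reported effect sizes will look smaller.

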## Discussion

BPD is a psychiatric disorder that leads to severe impairments in social interaction, self-harming and reduced quality of life. Several studies have shown neural correlates underlying symptom reduction after evidence-based psychotherapy treatment in patients with BPD [7–9]. Patients with BPD can experience distinct symptom alleviation from DBT, especially in terms of emotion regulation. Psychotherapeutic treatment of patients with BPD is characterized by a long treatment duration over several weeks [7]. The symptom pattern of patients with BPD (especially impulsivity) makes such a long treatment more difficult, in particular regarding acute fluctuations in symptom severity. Therefore, a treatment is necessary that facilitates these processes. While most rTMS protocols have a duration between 20 and 30 min, which, due to BPD symptoms, might complicate the recruiting of participants and enhance dropout rates, the iTBS protocol is both a safe and effective brain stimulation technique as well as economic and short. It therefore might adequately deal with the impulsivity aspect of patients with BPD and thus prevent dropout. A lesser dropout rate and a higher compliance can therefore be expected due to this decision. The limitation of the design being single blind instead of double blind is countered with surveying the patients' own assessment whether they are in the verum or sham condition, which is taking place after the first and the last iTBS session.

Brain stimulation techniques can possibly support the neural correlates of psychotherapeutic approaches. These techniques are well established in the treatment of other psychiatric disorders, especially depression [11]. In addition to that, first studies have shown that brain stimulation techniques can support symptom reduction in patients with BPD [15]. However, to our knowledge the combination of brain stimulation and evidence-based psychotherapy has not been examined to date. Our study aims to close this gap. For a first exploration of this research question, the manualized nature and regulated treatment duration of in-patient DBT makes it an appropriate choice for a first combination of iTBS and an evidence-based psychotherapy.

Due to the exploratory nature of our research question, the design will be conducted as a pilot study. It will provide evidence for feasibility and effect-size measures that allow for a data-based decision on the implementation, design and sample-size calculation of a confirmative multi-center trial. Our results might deliver answers to the questions if and how future studies should further investigate an enhancing effect of iTBS as an add-on to DBT or any other evidence-based psychotherapy in the treatment of BPD patients. Besides, we can identify necessary precautions and additional steps that can be taken to enhance the quality of further investigations. Furthermore, our study serves as an important addition to prospective investigations of DBT in a clinical setting itself.

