## Methods

### Procedure

Patients with BPD undergoing an 8–12-week routine inpatient DBT treatment in one specialized ward of a German psychiatric hospital are screened for eligibility after 4 weeks of DBT-treatment. After reaching informed consent they are additionally randomly allocated (1:1) to receive 20 sessions iTBS (DBT + iTBS) or 20 sessions placebo/sham stimulation (DBT + sham; each 1 per day from Monday to Friday) from the 5th to the 8th week of the treatment (see Fig. 1). Randomization procedure is based on an algorithm created with the programming platform MATLAB. Patients are blind regarding intervention (iTBS) or placebo (sham) whereas study personnel is not. Furthermore, data analyses will also be done blinded regarding group allocation.

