### Assessments

After successful study enrollment, before commencement of the stimulation, the following target parameters are recorded at baseline (see Table 1).

**Table 1 Tab1:** Assessment schedule throughout the study

Time	Screen-ing		Baseline	Treatment phase																				Post-intervention examination
Week				1					2					3					4					
Visit	T0			V1	V2	V3	V4	V5	V 8	V9	V10	V11	V 12	V 15	V 16	V 17	V 18	V 19	V22	V23	V24	V25	V26	T1
Day			− 3	1	2	3	4	5	8	9	10	11	12	15	16	17	18	19	22	23	24	25	26	26
MRI	X																							
Consent/information/data protection	X																							
Inclusion/exclusion criteria	X																							
SKID V PD	X																							
Mini-DIPS-OA	X																							
Psychiatric history	X																							
Medical history	X																							
Physical examination	X																							
Neurological Examination	X																							
MADRS	X												X											X
Pregnancy test	X																							
BSL-23			X					X					X					X						X
GAF			X																					X
BIS-15			X																					X
BDI-II			X					X					X					X						X
SCS-D			X																					X
Default motor threshold				X										X										

*Note*. T0 = baseline, V1–V26 = treatment phase, T1 = post-treatment

Short version of Borderline Symptom List (BSL-23) [42], second edition of Beck’s Depression Inventory (BDI-II) [43], Global Assessment of Functioning Scale (GAF) [44] and the Baratt Impulsiveness Scale, short form (BIS-15) [45]. Further, the German short version of the Self Compassion Scale (SCS-D) [46], the Montgomery–Åsberg Depression Rating Scale (MADRS) [47] and a Delay Discounting task [48] will be used (see detailed description below).

At the end of each week with iTBS/sham intervention, patients are asked to complete a BSL-23 and BDI-II questionnaire to assess symptom severity. Possible undesirable side effects of the stimulation are assessed and recorded by the practitioner after each treatment according to routine trial (serious) adverse events monitoring. At the end of the intervention period (after four weeks), further assessments are made for MADRS, GAF, BIS-15, SCS-D. Moreover, to check for a potential experimenter bias, participants’ belief about whether they took part in the verum or sham treatment condition are assessed after the first iTBS session and at post-intervention.

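### Asking patients to guess their arm does not counter single blinding: MADRS and GAF, which appear to be observer-rated, stay open to rater bias, and the depression conclusion should rest on BDI-II

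*Protocol article*

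**What the plan says.** On who is blind, the Procedure section of the protocol article states: "Patients are blind regarding intervention (iTBS) or placebo (sham) whereas study personnel is not". It adds: "Furthermore, data analyses will also be done blinded regarding group allocation". No separate or blinded outcome rater is mentioned.

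On the patient guess, the Assessments section says participants are asked which condition they believe they received, in order "to check for a potential experimenter bias". The Discussion goes further: "The limitation of the design being single blind instead of double blind is countered with surveying the" patients' own judgement of their condition, "which is taking place after the first and the last iTBS session".

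On the outcomes, the Secondary outcome measures section says: "As a secondary target criterion, the decrease in depression is recorded by the MADRS", alongside BDI-II. On functioning it says: "Improvement in general functional level in the verum vs. sham group is measured by the GAF". Table 1 schedules MADRS at screening, V12 and T1, and GAF at baseline and T1. The article describes BSL-23 as a self-rating and BDI-II as self-report. It gives neither description to MADRS or GAF.

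**The concern.** The trial is single-blind because personnel know the arm. The remedy offered collects information from the other party, the patient. A patient's guess carries no information on whether a rater who knew the allocation scored the iTBS arm more favourably, so the Discussion claims a protection that the design does not have.

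The Data analysis section treats secondary outcomes in the same way as the primary, with a time-by-group test at the 5% level. Improved depressive symptoms are part of the hypothesis in the Background. The Discussion also expects the pilot to supply effect sizes for planning a confirmatory multi-centre trial. A depression or functioning benefit on MADRS or GAF could therefore be reported, and carried into that planning, on the strength of ratings whose exposure to bias has been described as dealt with.

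**Working it through.** The plan states no figure on this point, so there is none to reproduce. The check sets the statements side by side; an illustration of size follows.

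**What each safeguard covers**

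1. *Patient blinding* (Procedure) protects scores that patients give themselves: BSL-23 and BDI-II.
2. *Blinded data analysis* (Procedure) protects analytic choices. It cannot alter a score already recorded by a rater who knew the arm.
3. *The patient guess* (Assessments, Discussion) shows whether safeguard 1 held. If unblinded staff gave cues, the guess may pick that up. It is a diagnostic and corrects nothing.
4. *Rater blinding* is stated nowhere. The only sentence on personnel says that they are not blind.

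**Which outcomes are left uncovered**

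| Outcome | How the article describes it | Ratings after the start of stimulation | Directly exposed to rater bias |
|---|---|---|---|
| BSL-23 (primary) | self-rating | weekly and T1 | no |
| BDI-II | self-report | weekly and T1 | no |
| MADRS | ten items with descriptive anchors, no self-report label | V12, T1 | yes, if rated by personnel |
| GAF | graded functional levels, no self-report label | T1 | yes, if rated by personnel |

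That MADRS and GAF are observer-rated is an inference from the missing label and from their anchors, which describe a person as seen from outside (needing to be persuaded to eat; danger to self or others). V12 matters as well as T1, because the Data analysis section models all assessed time points.

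**Illustration of size, on an assumed bias**

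Inputs from the article: 40 patients analysed, so 40/2 = 20 per arm; 53 enrolled, so about 26 per arm; two-sided alpha 0.05. Assumed, not in the article: no true effect, and a rating shift of d SD toward iTBS. With an assumed correlation of 0.5 between the two time points, the SD of change equals the SD of a single score, since √(2 × (1 − 0.5)) = 1. A two-sample t test on change stands in for the planned mixed model.

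Non-centrality = d × √(n/2). For n = 20 and d = 0.2 it is 0.2 × √10 = 0.632; for d = 0.4 it is 1.265. The degrees of freedom are 2n − 2 = 38. The rejection probability is the area of the noncentral t distribution beyond the two-sided 5% critical values.

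| Assumed shift d | 20 per arm | 26 per arm |
|---|---|---|
| 0.2 SD | 9.5% | 10.9% |
| 0.3 SD | 15.2% | 18.6% |
| 0.4 SD | 23.4% | 29.3% |

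With d = 0 the rate is 5%. The table follows wholly from the assumed shift.

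**The case against.** The strongest reply is that the article never says who rates MADRS or GAF. The sentence about personnel is general, and naming raters is a detail that an article commonly leaves to the full protocol. This stands: a reader might infer that unblinded clinicians are known to give these ratings, and the document does not establish that. It does not rescue the Discussion, however. Even if a fuller document named a blinded rater, the patient guess would not be what counters single blinding.

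Second, *experimenter bias* has a legitimate meaning here: staff who know the arm may pass cues to patients, and a patient guess does probe that. The Assessments section also says only that it checks. This stands, so the phrase needs clarifying rather than deleting.

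Third, the effect is limited. The primary outcome is self-rated by blinded patients, single blinding is openly disclosed, and the study calls itself an exploratory pilot. All true. A reader might infer that the primary result is compromised by unblinded raters; nothing in the article supports that.

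Fourth, the false-positive range is not evidence that bias exists. Agreed. Nor does the quoted GAF reliability of 0.54 to 0.66 help. A reader might take it as showing room for leniency, but reliability describes random disagreement and says nothing about a shift toward one arm.

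Fifth, the T1 guess may reflect how much the patient improved rather than loss of blinding. That is a caveat for interpretation and no reason to discard it: the first-session guess alone would miss cues given over the other 19 sessions.

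**Conclusion.** The point holds in a limited form. The Discussion is wrong to say that the patient guess counters the single-blind limitation; it checks patient blinding and nothing more. As the article stands, the MADRS ratings at V12 and T1 and the GAF rating at T1 are open to rater bias. This rests on two premises: that the general statement about unblinded personnel includes whoever rates these scales, and that both scales are observer-rated, which the article implies but does not say.

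The size of any bias is unknown. The 9.5% to 23.4% range at 20 per arm illustrates what an assumed 0.2 to 0.4 SD shift would do, and is not an estimate for this trial. What changes is how far a depression or functioning finding can be relied on: BDI-II can carry a depression conclusion under patient blinding, whereas MADRS and GAF alone cannot carry theirs unless their raters are shown not to know the arm.

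**What to change.** 1. In the Discussion, replace the claim that the limitation is countered. Say that the guess checks patient blinding only, and that the limitation remains for observer ratings.
2. In Assessments, clarify *experimenter bias* in the same sense: the guess looks for loss of patient blinding, including cues passed on by staff.
3. State who rates MADRS and GAF and whether they have access to the allocation.
4. Base the depression conclusion on BDI-II. Report MADRS and GAF as open-rater supportive results, unless all their post-randomisation ratings (MADRS at V12 and T1, GAF at T1) are made by existing staff without access to the allocation.
5. Report the guess by arm at both time points, noting that the T1 guess is confounded with improvement.

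Items 1 to 3 and 5 are wording and reporting, and item 4 needs no new data. The cost is that MADRS and GAF carry less weight. Reassigning the ratings is optional. The documents do not show that staff unaware of the allocation are available, and since inclusion began in January 2021, changing raters part-way could add between-rater variation.
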